### Harms

Any spontaneously reported adverse events and other unintended effects of trial interventions or health status changes (absolute contraindication for PA) should be immediately reported by the participants, the exercise or the healthcare professionals to the principal researcher.

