### Strategies to improve adherence to interventions

Exercise professionals will monitor adherence to the intervention by recording the number of sessions attended over 12 weeks. Motivational strategies include organising online group meetings, sending weekly WhatsApp and Instagram reminders, providing access to resources promoting an active and healthy lifestyle and offering access to the YouTube channel.

The overall focus of these sessions is based on what already motivates participants to increase or maintain their PA level and healthy lifestyle. This is achieved by fostering interaction among participants to create meaningful group processes, such as support, experience exchange and reflection, as well as collecting feedback regarding the exercise programme and resources. All monthly online sessions will last 20–30 min and are led by exercise and health professionals. These sessions aim: (1) to inform about PA guidelines, benefits associated with PA and possible ways to increase PA during pregnancy; (2) to discuss participant’s barriers, wishes, needs, knowledge and former PA experiences to identify individual characteristics and motivation towards a more physically active lifestyle; (3) to teach the advantages of using a PA tracker, aside from measuring the PA level, the activity trackers are also used as an intervention element to motivate the participants to increase their PA levels, share it on a Strava group and provide feedback on recent PA performances; (4) to collect feedback regarding the organisation of the exercise programme and (5) to discuss other relevant topics chosen by the participants, such as myths about pregnancy PA, postpartum PA, the pelvic floor, uterine contractions, abdominal muscles and diastasis recti, birth, etc.

Individual sessions will be scheduled during the daytime at a time that is as convenient as possible for the participant.

The primary objectives of these motivational strategies are to enhance participant retention and adherence to follow-up, as well as to incorporate a patient-centred approach into the exercise intervention.

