### Outcomes

Primary, secondary and additional outcome measures, including the specific measurement variables, timeframe and instruments, are shown in table 2.

**Table 2 T2:** Primary, secondary and additional outcome measures, including the specific measurement variables, timeframe and instruments

Outcome measures	Instruments
Primary outcome measuresTimeframe: baseline (week 0) and after 12-week intervention (weeks 13 and 14)Analysis metric: change from baseline	
PA level and pattern of PA in the type of PA (work, active commuting, exercise, etc.), type of exercise, duration of each session (time spent in PA), weekly frequency and intensity and weekly volume (MET-min/week).	PPAQ^21^ and get active questionnaire for pregnancy^22^
Self-perceived fitness: self-perceived global fitness and fitness components (cardiorespiratory, strength, speed/agility and flexibility) when compared with other women of the same age. Likert scale 1 (poor) to 5 (very good).	IFIS^23^
Cardiorespiratory fitness estimated in mL/kg/min	Cardiorespiratory fitness—6-min walk test (average distance covered in metres and estimated cardiorespiratory fitness in mL/kg/min)^24^https://youtu.be/CUaFgfdSObc
Upper limbs strength	Upper limb strength—wall push-ups (number of repetitions in 30 s)^6 17^https://youtu.be/dp_tRoyxVYU
Lower limbs strength	Lower limb strength—sit-and-stand (number of repetitions in 30 s)^6 17 25^https://youtu.be/3ihcqnzyTXk
Dynamic balance	Dynamic balance—superwoman^6 17^https://youtu.be/Xiv_vWpe4-A
Static balance	Static balance—one-leg stance^6 17^https://youtu.be/sr0eYCfbLiM
Lower limbs flexibility	Lower limbs flexibility—modified sit and reach (mm)^6 17^https://youtu.be/Y6y_FAa3ulk
Upper limbs flexibility	Upper limbs flexibility—back scratch (mm)^6 17^https://youtu.be/MBwKi8kSFx8
Agility	Agility—time up and go over 3-m distance (in min)^6 17^https://youtu.be/3C944cMuTFo
Secondary outcome measuresTimeframe: baseline (week 0) and after 12-week intervention (weeks 13 and 14)Analysis metric: change from baseline	
Sleep quality	PSQI^26^
Weight prepregnancy, weight at baseline and weight gain (kg)	Body weight: measure with the participant wearing light clothing and without shoes^27^
Happiness scale	SHS^28^
Depression scale	EPDS^29^
Adherence to the Mediterranean diet	MEDAS^30^
HR	Measured rest HR, estimated maximal HR and calculated target HR (beats per minute)

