Prevalence of pregnancy-related symptoms and health parameters (eg, weight gain, blood pressure, prevalence of gestational diabetes or hypertension and contraindications for PA)	Medical records, pregnancy symptoms inventory and get active questionnaire for pregnancy^22^
Other prespecified outcome measuresTimeframe: after the intervention (13 and 14 weeks)	
Participant satisfaction with the available resources—Likert scale (1–5, with 1 not satisfied at all, and 5 highly satisfied).	Satisfaction with educational digital resources (ie, ACTIVE PREGNANCY Guide, YouTube channel ACTIVE PREGNANCY and the framework of the ACTIVE PREGNANCY app).
Participant satisfaction with the intervention—Likert scale (1–5, with 1 not satisfied at all, and 5 highly satisfied).	A questionnaire explicitly made for the intervention evaluating different domains: type of exercises, hardness of the sessions, difficulty in particular exercises, weekly frequency, duration of the sessions, context of intervention (online, outdoor, gym and hospital), satisfaction with the exercise physiologist, willingness to continue in postpartum, willingness to repeat in future pregnancy and overall satisfaction to be included in the programme.
Feasibility and adherence	Feasibility evaluation of the implementation of the exercise programme: (1) number of women who declined to participate in the study; (2) number of women who gave up participation in the study; (3) adherence to the programme (number of days of actual performance of the exercise programme while admitted) and (4) number of women who completed at least 80% of the study.

EPDS, Edinburgh postpartum depression scale; HR, heart rate; IFIS, International Fitness Scale; MEDAS, Mediterranean Diet Adherence Screener; MET, metabolic equivalent; PA, physical activity; PPAQ, pregnancy physical activity questionnaire; PSQI, Pittsburgh sleep quality index; SHS, subjective happiness scale.

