### Plans to promote participant retention and complete follow-up

Plans to promote retention include the above-mentioned motivational strategies. Moreover, they will be informed about the study’s objectives and dissemination plans. Participants who discontinue or deviate from intervention protocols will be contacted by telephone to provide qualitative feedback and help us understand context-specific issues.

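### Adverse events outside the Table 2 instruments are captured by spontaneous report only, which risks undercounting and possibly unequal ascertainment between the in-person and online arms, in an unknown direction

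*Protocol article*

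**What the plan says.** The Harms section of the protocol article is one sentence. Its scope is "Any spontaneously reported adverse events and other unintended effects of trial interventions", together with changes in health status, and these "should be immediately reported by the participants, the exercise or the healthcare professionals to the principal researcher". So there are three reporting routes and a rule of immediate reporting, but the starting point is that someone volunteers the event.

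Four other sections bear on this:

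- **Outcomes, Table 2.** A secondary outcome is "Prevalence of pregnancy-related symptoms and health parameters (eg, weight gain, blood pressure, prevalence of gestational diabetes or hypertension and contraindications for PA", drawn from "Medical records, pregnancy symptoms inventory and get active questionnaire for pregnancy". The timeframe for secondary outcomes is "baseline (week 0) and after 12-week intervention (weeks 13 and 14".
- **Strategies to improve adherence.** "Exercise professionals will monitor adherence to the intervention by recording the number of sessions attended over 12 weeks". Attendance is the only thing this section has staff record at each session.
- **Retention.** "Participants who discontinue or deviate from intervention protocols will be contacted by telephone"; the stated purpose of the call is qualitative feedback, and harms are not mentioned.
- **Table 1 and the randomisation and blinding section.** Supervision is in person in one arm and through a virtual platform, with the woman at home, in the other. Participants, healthcare providers and outcome assessors are unblinded after assignment.

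**The concern.** Passive reporting records what is noticed and then volunteered. It usually undercounts, most of all for minor or transient events. In this trial the chance of being noticed may also depend on the arm. An instructor in the room and one watching a screen do not have the same view of a stumble or a dizzy spell. Equally, a woman at home may be more or less inclined to mention a symptom than one in a group class.

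The article says its findings should help exercise professionals deliver safe programmes and should inform practice on virtual training. Readers will therefore set the two arms' event counts side by side whether or not a test is planned. If capture differs by arm, that reading mixes true risk with how events were found. If capture is equally low in both, the contrast survives as a ratio but the absolute burden is understated.

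**Working it through.** The article gives no event rate, capture rate or safety power, so there is no figure to reproduce. The check has two parts.

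**1. Is there another route that captures events during training?**

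- *Table 2 instruments.* These are structured and apply to both arms, but are scheduled before and after the programme. They name symptoms, weight gain, blood pressure, gestational diabetes or hypertension, and contraindications. No item is named for exercise-related injury or events in sessions. Medical records can cover the interval, but only for events that reached care.
- *Routine care.* The Recruitment section lists appointments at weeks 6–10, 25 and 32. The programme lasts 12 weeks from a start at week 13 to 20, so it ends at week 25 to 32. Week 25 falls in every woman's interval (13 + 12 = 25). Week 32 falls in it only for a start at week 20 (20 + 12 = 32). Most women therefore have one listed routine visit between start and finish.
- *Session contact.* 2 sessions × 12 weeks = 24 per woman; × 100 women = up to 2,400 woman-sessions per arm. Staff are in live contact each time, but only attendance is described as recorded.
- *Women who stop.* Anyone completing less than 80% of sessions is counted as lost to follow-up. 0.80 × 24 = 19.2, so a woman with 19 sessions or fewer is in that group. A woman who stops because of an event is likely to be in it and may miss the post-test. The call to her has no stated harms question.

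**2. What could unequal capture do?**

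Observed risk = true risk × capture probability. With equal true risk in both arms, the observed online/in-person ratio is capture online ÷ capture in-person, whatever the true risk. Inputs: 100 women per arm (Sample size section). The 15% true risk and all capture rates are assumptions, chosen to show a range; 15% gives 15 true events per arm and 30 in all.

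| Assumed capture, in-person / online | Observed per 100, in-person / online | Ratio online/in-person | Missed of 30 |
|---|---|---|---|
| 80% / 80% | 12 / 12 | 1.00 | 6 |
| 50% / 50% | 7.5 / 7.5 | 1.00 | 15 |
| 60% / 50% | 9 / 7.5 | 0.83 | 13.5 |
| 80% / 50% | 12 / 7.5 | 0.63 | 10.5 |
| 60% / 80% | 9 / 12 | 1.33 | 9 |

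For example, 0.15 × 0.80 = 0.12 and 0.15 × 0.50 = 0.075, and 0.075 ÷ 0.12 = 0.625. In the other direction, 0.80 ÷ 0.60 = 1.33. Undercounting appears in every row. Distortion between arms appears only when capture differs, and its sign depends on which arm captures more.

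**The case against.** The other side has four good arguments.

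- **Harms do not rest on spontaneous reports alone.** Table 2 uses records and structured instruments in both arms. This stands, and it limits the point to events outside those instruments.
- **Both arms have live supervision by qualified physiologists, and three parties may report.** Two of the three routes do not depend on who is in the room. This also stands: unequal capture is a credible risk, not an established fact.
- **No between-arm comparison of adverse events is stated.** The statistical methods section compares primary and secondary outcomes, and adverse events as such are not in Table 2. A reader might infer that a planned safety comparison is biased, or that the online arm will look safer than it is. The documents support neither: no such comparison is described, no capture rates are given, and the table above shows that the sign can go either way.
- **A journal article leaves forms and call scripts to the full protocol.** True of forms, but the point does not rest on their absence. The Harms section itself names spontaneous reporting as the method, and the sections on session records and the telephone call state other purposes.

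It is also fair that a question at each session reaches only women who attend, and is put face to face in one arm and by video in the other. It narrows the gap without closing it.

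**Conclusion.** The point holds in a limited form. For adverse events outside the Table 2 instruments, the stated method is spontaneous report. In an open trial whose arms differ in the physical presence of the supervisor, that risks undercounting and possibly unequal ascertainment, in a direction the documents do not settle. What is exposed is the descriptive event counts by arm, not a planned test.

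The size cannot be estimated from the article. Under the assumed capture rates, the observed ratio ranges from 0.63 to 1.33 when the true ratio is 1. The illustration rests on equal true risk in both arms and on capture rates that have no source in the document. The change is worth making because the contacts it needs already exist.

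**What to change.** In the Harms section, keep immediate reporting as it is and add one short, fixed adverse-event question set, worded identically for both arms. Ask it:

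1. at each session, logged with attendance;
2. at the post-test;
3. in the telephone call already planned for women who stop or deviate.

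Report events descriptively by randomised arm for all randomised women, including those below 80% attendance.

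Recruitment was due to start in May 2025, so introduce the questions on the same date in both arms and report that date. Counts before and after it can then be read separately.

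Cost: about one extra item per session, plus an addition to the post-test form and the call script; no new visit or procedure. More minor events will be recorded. Women who do not attend are reached only through the post-test and the call, so the call should ask the same questions.

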### Sample size

The sample size was determined using G*Power software (V.3.1) based on previous studies. To detect statistical differences between pre- and postdifferences in one group, a sample of 36 pregnant women was considered based on calculations performed using G*Power with the inputs of the mean±SD from previous studies by Dennis *et al*,^19^ a power of 0.8 and α≤0.05. Additionally, to detect statistical differences between two independent groups of pregnant women included (experimental) or not (control) in exercise programmes, a sample size of 59 per group was calculated based on the mean±SD values from previous studies by Ramírez-Vélez *et al*,^20^ a power of 0.8 and α≤0.05. Based on an expected loss-to-follow-up rate of 20%, we plan to include 100 participants in each of the two intervention groups. Therefore, a total of 200 pregnant women will be recruited and randomly allocated to either the IN or ON group (100 per group).

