We hypothesised that a multicomponent supervised prenatal physical exercise programme previously described in Santos-Rocha *et al*’s study^14^ positively impacts PA, fitness, lifestyle and health parameters of women throughout pregnancy, regardless of the delivery environment (in-person (IN) *vs* online (ON)), maternal age or weekly volume of PA, and that both exercise environments are equally effective.

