### Trial design

This is a multicentre, two-arm, parallel-group, randomised controlled trial (RCT) with a 1:1 allocation ratio and an equivalence framework. Pregnant women will be randomly assigned to either an IN or ON supervised multicomponent exercise intervention.

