### Statistical methods for primary and secondary outcomes

Demographic data (age, weight, gestational age, area of residence and date of birth) will be described using frequencies and percentages for categorical variables.

Descriptive statistics (mean, SD, median and IQR) will be used to summarise baseline characteristics of participants in both groups (IN and ON).

Descriptive and inferential statistics will be applied to all outcomes.

A comparative analysis of IN *versus* ON interventions will be conducted using both intention-to-treat and per-protocol approaches. Comparative analysis will be used to compare changes in primary and secondary outcomes between IN and ON groups over time (baseline and postintervention). Subgroup analyses will evaluate potential differences between maternal age groups (<35 *vs* 35+ years) and PA level groups.

Adherence to the intervention (proportion of attendance in the planned sessions) will be calculated after the postintervention assessments.

Data from participants who do not complete at least 80% of the scheduled sessions will be considered a loss to follow-up.

Regarding additional outcome analysis, the evaluation of interventions and resources will be performed through descriptive analysis, summarising satisfaction with resources and exercise interventions.

Continuous variables will be assessed for normality using Shapiro–Wilk tests. Normally distributed variables will be presented as mean±SD and analysed using the independent sample t-test. The non-normally distributed data will be reported as the median with IQR and will be analysed using the Mann–Whitney test. For the within-group difference, normally distributed variables will be calculated with the paired-sample t-test. In contrast, those non-normally distributed variables will be calculated with the paired-sample non-parametric Wilcoxon test. Categorical data will be analysed using Pearson’s χ^2^ test or Fisher’s exact test, as appropriate.

A significance level of 0.05 (alpha level) will be set for all statistical tests. Power calculations were performed to ensure that the study was adequately powered to detect clinically significant differences between groups. All statistical analyses will be conducted in Statistical Package for the Social Sciences.

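### The only two-group sample-size calculation is for exercise versus no exercise, not in-person versus online equivalence, so power for the randomised comparison is not shown; 59 per group with 20% loss also gives 74, not 100

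*Protocol article*

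**What the plan says.** All references are to the protocol article.

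- **Design.** The Trial design section describes a "two-arm, parallel-group, randomised controlled trial (RCT) with a 1:1 allocation ratio and an equivalence framework", with women "randomly assigned to either an IN or ON supervised multicomponent exercise intervention". The Discussion again calls it an equivalence trial. Table 1 gives both arms the same type, duration, frequency and intensity of exercise; supervision mode and setting differ.
- **Hypothesis.** The introduction ends with the hypothesis that "both exercise environments are equally effective".
- **Sample size, one group.** A pre–post calculation gives 36 women.
- **Sample size, two groups.** The stated aim is to detect a difference between two independent groups: for "pregnant women included (experimental) or not (control) in exercise programmes, a sample size of 59 per group was calculated", using means and SDs from earlier studies, with power 0.8 and alpha at most 0.05. No endpoint, mean, SD or sidedness is given.
- **Inflation.** "Based on an expected loss-to-follow-up rate of 20%, we plan to include 100 participants in each of the two intervention groups", making 200 in total.
- **Claim of adequacy.** The statistical methods section says: "Power calculations were performed to ensure that the study was adequately powered to detect clinically significant differences between groups".

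**The concern.** Neither randomised arm goes without exercise. The size of an exercise-versus-none effect does not tell us how precisely two exercise arms can be compared with each other, nor how small a difference between them could be ruled out. An equivalence trial is sized from a margin and an expected difference near zero; a difference trial is sized from an effect it hopes to detect. The Sample size section does the second, for a different pair of groups, and the methods section then presents the result as adequate for the groups randomised.

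What is at stake is the reading of the final result. The between-group tests named in the methods section are difference tests (t-test or Mann–Whitney). If such a test is non-significant, the hypothesis of equal effectiveness invites a conclusion of equivalence. The sample-size rationale should show what difference 200 women can exclude, and as written it answers another question.

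The step from 59 to 100 is a smaller matter: it is attributed to 20% loss, and 20% loss does not produce it.

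**Working it through.** **1. The plan's own figure.** The 59 per group cannot be reproduced, because the mean, SD and endpoint come from a cited study and are not given. Solving a two-sample t-test backwards (59 per group, power 0.80, alpha 0.05) shows the standardised difference it implies. By normal approximation d = (z for alpha + z for power) × √(2/59):

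- two-sided: (1.960 + 0.842) × 0.184 = 0.516; exact t calculation 0.52
- one-sided: (1.645 + 0.842) × 0.184 = 0.458; exact t calculation 0.46

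Sidedness is not stated, so both are shown.

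**2. The inflation step.**

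- Standard: 59 / (1 − 0.20) = 73.75, so 74 per group (118/0.80 = 147.5, so 148 in total)
- Common shortcut: 59 × 1.20 = 70.8, so 71
- From the one-group figure: 36/0.80 = 45
- From both added: (36 + 59)/0.80 = 118.75, so 119

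None gives 100. Going from 59 to 100 would correspond to 1 − 59/100 = 41% loss. In the other direction, 100 with 20% loss leaves 80 evaluable per arm.

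**3. What 80 per arm gives for a difference test.** At the implied difference (0.52 two-sided or 0.46 one-sided), power is about 90% in either case.

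**4. What 80 per arm gives for equivalence.** Assumptions: two one-sided tests, normal approximation, true IN–ON difference of zero, and a margin Δ in units of the SD of the change score (Table 2 gives change from baseline as the analysis metric). The margins are illustrative, because the article states none.

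Power = 2Φ(Δ/√(2/n) − z) − 1, set to zero if negative, with √(2/80) = 0.1581.

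Worked example, Δ = 0.4, one-sided 5%: 0.4/0.1581 = 2.530; 2.530 − 1.645 = 0.885; Φ = 0.812; power = 0.624.

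| Margin (SD of change) | Power, one-sided 5% | Power, one-sided 2.5% |
|---|---|---|
| 0.3 | 20% | about 0% |
| 0.4 | 62% | 43% |
| 0.5 | 87% | 77% |

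Smallest margin with 80% power at 80 per arm: (z + 1.2816) × 0.1581.

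- one-sided 5%: (1.645 + 1.282) × 0.1581 = 0.46 SD
- one-sided 2.5%: (1.960 + 1.282) × 0.1581 = 0.51 SD

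**5. Evaluable number needed per arm for 80% power.** n = 2 × ((z + 1.2816)/Δ)², with the number to randomise at 20% loss in brackets.

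| Margin | One-sided 5% | One-sided 2.5% |
|---|---|---|
| 0.3 | 191 (239) | 234 (293) |
| 0.4 | 108 (135) | 132 (165) |
| 0.5 | 69 (87) | 85 (107) |

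Whether 100 per arm is enough therefore depends on the margin.

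**The case against.** Several objections have force.

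- **The 36-woman calculation is not misplaced.** The abstract asks whether the programme maintains or improves maternal parameters over 12 weeks, and the methods plan paired t-tests or Wilcoxon tests within groups. A one-group pre–post calculation fits that aim. This stands. It simply does not size the randomised comparison.
- **The power of a t-test does not depend on what the arms are called.** With 80 evaluable per arm, a standardised difference of about 0.5 would be detected with about 90% power, whichever groups are compared. This stands too, so the adequacy statement should be called not shown rather than false. What is missing is any reason why a difference taken from exercise versus no exercise is the relevant one for IN versus ON.
- **100 is more than 74.** The inflation mismatch is an excess. A reader might infer that it costs power; it does not.
- **A margin may be in a full protocol or analysis plan that is not shown.** This is fair, and the absence of a margin from the article is not the finding. The article does state the basis of its sample size, and that basis conflicts with its own design. A margin held elsewhere would not change this.

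**Conclusion.** The point holds. The only two-group calculation concerns a contrast that the trial does not contain and a difference hypothesis that its equivalence framework does not pose. The statement of adequate power is therefore not shown for IN versus ON. The step from 59 to 100 is a secondary wording error: 20% loss gives 74, and the further 26 per arm are unexplained.

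A reader might infer that the trial is underpowered. The document does not support that. At a margin of 0.5 SD, 80 per arm gives 77% to 87% power. At 0.4 SD or less it falls below 80% (43% to 62% at 0.4 SD). Without a stated margin neither conclusion can be drawn.

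The figures rest on a true difference of zero, a normal approximation, margins chosen for illustration in SD of the change score, and 80 evaluable women per arm. The last could fail: the data collection and statistical methods sections count women who complete under 80% of sessions as lost to follow-up, and if that rule removes more than 20%, power is lower than shown.

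**What to change.** Keep 200 women and change the text.

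1. Restate the Sample size section for IN–ON equivalence: 100 randomised per arm, 80 evaluable after 20% loss.
2. Set the equivalence margin on clinical grounds, in the units of the outcome or outcomes that carry the equivalence claim (Table 2 lists ten primary measures), and say that the SD used is that of the change from baseline. Report beside it the power that 80 per arm gives. The values of 0.46 SD (one-sided 5%) and 0.51 SD (2.5%) describe achievable precision; they should not be adopted as margins because they fit the sample.
3. Keep the 36-woman calculation if it is labelled as supporting the within-group pre–post analysis.
4. Label the 59-per-group calculation as background, or correct its inflation to 74 and state that 100 is a deliberate excess.
5. Reword the power sentence in the statistical methods section so that it refers to the equivalence comparison and to what the sample can show.

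The cost is wording and one recalculation, with no added participants. Depending on the margin, the stated power may be less favourable than the text now suggests.
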